### Study procedures

***Part 1: Developing an informational masking measurement test and determining its validity.*** When studying the informational masking, use of the coordinate response measure (CRM) has been frequently been introduced as one of the most popular speech materials for evaluating informational masking
^24^. In these sentences, the same rigid structure with “Ready [call sign] go to [color] [number] now” format is used. In these sentences, eight call signs, four colors, and eight numbers from 1 to 9 can be used. These sentences will be expressed by speakers of different genders
^24,
25,
27^. In the present study, 256 sentences will be created for each speaker (8*4*8). Sentences will be expressed by eight speakers (four women and four men), providing a total of 2048 sentences. Although CRM stimuli have been initially designed to measure the speech perception in the presence of competing signals, these speech materials provide no contextual information; i.e. predicting the given color or number in the phrases is not possible. This is an important factor in measuring informational masking
^25^.

Since there is no Persian version of these sentences, this research will prepare the sentences and determine their content and face validity and reliability. Then, after selecting the nouns, colors, and numbers used in the sentence, conforming to the main English version, the prepared sentences will be given to experts in this field (audiologists, speech therapists, and linguistics) to determine the content validity. These experts are the academic members of rehabilitation schools of IUMS, Tehran University of Medical Sciences (TUMS) and Shahid Beheshti University of Medical Sciences (SBUMS). These experts will be emailed a questionnaire to score the validity items (see
Table S1, Extended data).

After selecting the best pattern matching Persian language, based on the model presented for recording the sentences, all sentences will be recorded in a studio with the eight speakers. In order to record the sentences, all criteria of the English version including the sampling rate of 44.1 kHz and giving 3s to speakers to produce each sentence will be followed. Then all the sentences will be scaled and all the words in CRM will be set such that they occur simultaneously, called coordinate sentences
^25^ where each of the sentences will be filtered using a band pass filter of 80 to 8000 Hz filter. Again, in order to determine the face validity, the recorded sentences will be given to the experts mentioned above to determine their suitability. They must fill the questionnaire, which will be emailed to them.

To determine the reliability of CRM speech materials, the mean scores of CRM recognition in the silent will be evaluated in a group of young and old people with normal peripheral hearing who do not have speech perception difficulties in noisy environments. There will be one preliminary test and then a re-test. This evaluation will be implemented at the comfort hearing level of the participants. The score will be calculated based on the correct recognition percentage of the sentences. A sentence will receive a correct score when the color-number combination recognition is recognized correctly
^25,
27^. In this study, the mean correct score for color, number, and noun will be studied separately in order to calculate the error percentage for each of them
^24^. By preparing these sentences, they can be used in the part 2 of the study.

The best way to measure informational masking score is determining the score for speech recognition in the presence of meaningful and meaningless competing noise. To this end, the recognition score for Persian version of CRM speech corpus will be measured under two conditions:

**A.**
*In the presence of meaningful competing noise:* The competing signal will be selected from the Persian version of CRM corpus, where the call sign, color and number used in the competing sentence will be different from those of the target sentence and it will be expressed by a different speaker. The individual will be trained to pay attention to certain target call signs and ignore other signals
^24,
25,
27^. As one of the important effective factors for informational masking is the great similarity between target and competing signals (like when both of them are speech)
^7,
8^, using CRM sentences as both the target signal and competing signal, the high semantic and syntactic similarity would develop between target and competing signals
^24,
25^.
**B.**
*In the presence of meaningless competing signal:* the previous signal will be manipulated such that its spectrum content remains fixed but meaningless - indeed, energetic masking will remain but informational masking will be reduced. "Time-reversed speech" will be used for this purpose. This is one of the most effective methods in behavioral and neurophysiological research performed for the effects of speech signals on each other. In this method, by fixing the long-term acoustic spectra of two signals and manipulating one of them such that it divides into non-overlapping time segments, and with reverse time presentation of each segment connecting them to each other, we will have a signal which is equal with the first signal in terms of the spectrum but is not understandable
^28^. In the case of using 20–40 millisecond time windows, this method does not have significant effectiveness in non-understanding the speech signal; therefore, longer time windows should be used
^28^. MATLAB R2018 software will be used in constructing this signal.

The intensity setup of the speech signals with two competing talkers used were similar to some previous studies
^29^. The overall level (RMS power) of target CRM was fixed at the 60 dBSPL. The overall level (RMS power) of each masker was adjusted relative to the target’s level to produce one target-to-masker ratios (TMRs). Initially the masker level was varied in 4 dB steps and then they varied adaptively in 2 dB steps. The two CRM masker phrases always had the same RMS power. The TMRs in sentence recognition test in steps A and B was ±8, ±4, and 0. The target signal is always presented from a loudspeaker in the 0-azimuth degree and two competing signals from the loudspeakers, which are at ±45 and ±90 degree and 0 azimuth degree (once with spatial separation and twice in the direction of target signal), where once the competing signal has the same gender as the target signal and another time has a different gender. As a result, 30 conditions will be evaluated at each step (5 TMRs and three spatial angles with two different genders).

Finally, the informational masking score in all 30 conditions will be calculated as follows:

Speech recognition score in the meaningful competing noise condition-speech recognition score at non-understandable noise condition=informational masking score (percentage).

Jakien and Gallun provided mathematical equations by which the effects of age can be predicted for 45 degrees of separation
^30^. We will develop similar equations, compare them with the published equations, and will use these normative functions to assess improvements in performance after training.

In this step of the research, construct validity will be used to determine the validity of the test. For this purpose, Speech, Spatial, and Qualities of Hearing Scale (SSQ) questionnaire score of each individual will be compared against the informational masking score
^31^.
Figure S1 (Extended data) represents the participant’s timeline of the first part of the study.

***Part 2: the effect of auditory spatial training on the informational masking release.*** This part of research will be conducted in three steps: before auditory spatial training, during training, and after training.

**1. Assessments prior to auditory spatial training (preliminary interview)**

**-**Obtain patient history to confirm the inclusion and exclusion criteria of the participants
**-**Initial clinical examination, including otoscopy and tympanometry
**-**Perform pure tone audiometry test
**-**Perform MMSE questionnaire to ensure lack of salient cognition problem in the participants
^26^

**-**Determine speech perception difficulties in the presence of noise: this was evaluated with a question:
*Do you have difficulty in understanding speech in noisy situations?* There were three response options: yes, no or sometimes. Those who responded yes were entered into the study.
**-**Measure informational masking score using the test constructed in Part 1 (primary outcome)
**-**Measure synthetic sentence identification test (secondary outcome)
^32^

**-**Determine the SSQ score
^31^. The SSQ self-assessment questionnaire will be filled out by the researcher during the preliminary interview. As improving informational masking can improve the speech perception quality of people, this questionnaire will be used to measure the speech perception quality of the participants quantitatively (secondary outcome).
**-** The temporary storage and manipulation of information required to perform a wide range of complex cognitive activities such as learning, and reasoning called working memory. Since the working memory have more influences on the informational masking tasks, so we will measure the ‘Persian Reading Span test’ score in our study
^33^. Participants will asked to read sets of sentences, report on the semantic acceptability of each sentence, and then recall the final word of each sentence (secondary outcome).

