### Study design, setting and participants

This research will be conducted in the Audiology Clinic of Rehabilitation School of Iran University of Medical Sciences.

This study consists of two main parts. Part 1: develop and determine an informational masking measurement test and explain its validity characteristics in a test development study, conducted cross-sectionally. The study population will be a group of elderly (60 to 75 years old) and a group of young (20 to 40 years old) people. The young people will be recruited from rehabilitation students of Iran University of Medical Sciences, while elderly people are those referred to the audiology clinics of Iran University of Medical Sciences.

Part 2 (simple randomized clinical trial): the effect of training on informational masking release. This part of study is a simple randomized clinical trial design and patients will be randomly assigned into two groups of control (not receiving auditory spatial training) and intervention (receiving auditory spatial training). The random allocation will be performed based on balanced randomization [1:1] where the allocation will be applied by random number table (those assigned an odd number, control group; those assigned an even number, intervention group). This allocation sequence will be generated by one of the audiology clinic staff of the IUMS who will not have any role in the study. An elderly population, 60–75-years-old, who are referred to the audiology clinics of Iran University of Medical Sciences will be selected. The two groups will be matched for age and gender. Those in the control group will not receive any rehabilitation programs during the study.

*Inclusion criteria (for all participants in the study):* auditory thresholds ≤25dB within the 250–8000Hz frequency range for ensuring the normal pure tone audiogram or normal peripheral hearing, ensuring lack of salient cognitive problems using Mini Mental State Examination (MMSE)
^26^; having diploma or higher degree; right-handedness (using Edinburgh handedness inventory); speaking Farsi and being monolingual; complaint about speech in noise perception difficulties (just for those in part 2 of the study); and normal condition of middle ear function.

*Exclusion criteria (for all participants in the study):* unwillingness for participation in each step of research and not meeting inclusion criteria.

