**3. Assessments after auditory spatial training (interview immediately after and five weeks after training)**

The informational masking test (as per Part 1) will be done immediately after training and five weeks after that using the Persian list of the coordinate response measure (CRM) corpus, which will be compared with the pre-training results (preliminary interview). This score will be the primary outcome. The reason for repeating experiments five weeks after the intervention is determining the reliability of the results obtained by intervention for informational masking release.

The informational masking release value will be calculated based on the difference between sentence recognition score (in all 30 conditions of signal to noise, different spatial angles, and two genders) in both noise situations (meaningful and non-understandable). The changes in informational masking in the assessments will be calculated before and after the intervention across all 30 conditions (see
Table S2, Extended data).

The ‘synthetic sentence identification test’
^32^ and the ‘Persian Reading Span test’ score
^33^.also will be evaluated immediately after training and 5 weeks after that.

As the ultimate purpose of this research is improving the quality of speech perception of elderly people, the score of SSQ immediately and 5 weeks after intervention will be obtained and the results of both intervention and control groups will be compared separately. This score and the scores of ‘synthetic sentence identification test’ and ‘Persian reading span test’ will be the secondary outcomes of the interventions.
Figure S2 (Extended data) represents participant’s timeline of the second part of the study.

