### Ethical statement and consent to participate

The Medical Ethics Committee of Iran University of medical sciences approved the study protocol (IR.IUMS.REC.1397.303) and the ethical principles of the ethics committee will be observed in this research. Researchers will send any amendments to the protocol in the future to the ethics committee.

One of the researchers of this study will obtain written informed consent from patients willing to participate in the trial (see Extended data). The purpose of the research and its steps will be explained for all participants before the study start. Confidentiality of data and results of tests will be ensured to participants. Participants will be made aware that they can refrain from cooperation in the study when they want. Conducting tests has no side-effects for the studied individuals and all tests and training sessions will be without cost to the participants.

Since this will be the first time of performing this training, we will running a focus group and asking our participants what they will think of the intervention and how likely they will continue performing the auditory training in the future.

To promote participant retention and complete follow-up, in every training session the examiner will provide feedback to all participants and will inform them about the training progress. The researcher will ask them about the impact of training on the participant’s daily communication conversations. Also at the first of each training session the initial level of training will be calculated and if there will be a progress in the initial signal to noise ratio which train will be started from that, the examiner will inform the patient.

All data will be entered into forms which are prepared for data collection (see
Table S2; Extended data) and the participant files will be stored at study site and will be maintained in a secure place and manner. Participant files will be maintained in storage for a period of 2 years after completion of the study. Only Principal Investigators will be given access to the study data.

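### Only trained participants are asked about everyday benefit before the self-report SSQ is compared between arms, so the SSQ difference may partly reflect prompted reporting

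*Protocol article*

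**What the plan says.** The protocol article spreads the relevant statements over five sections.

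- **Baseline SSQ** (Assessments prior to auditory spatial training): "The SSQ self-assessment questionnaire will be filled out by the researcher during the preliminary interview". The scale is used to quantify participants' quality of speech perception.
- **Follow-up SSQ** (Assessments after auditory spatial training): "the score of SSQ immediately and 5 weeks after intervention will be obtained", and the two groups are compared. The section heading describes these visits as "interview immediately after and five weeks after training". The section does not say who completes the form.
- **Status of the SSQ** (same section): "This score and the scores of ‘synthetic sentence identification test’ and ‘Persian reading span test’ will be the secondary outcomes of the interventions". The reason given for measuring it is that "the ultimate purpose of this research is improving the quality of speech perception of elderly people".
- **Contact during training** (Ethical statement and consent to participate): as a retention measure, the examiner gives feedback on progress in every training session. The next sentence begins "The researcher will ask them about the impact of training on the" and goes on to participants' everyday conversations. The section also plans a focus group on what participants think of the intervention, with no timing given.
- **Who has this contact**: the section on providing the training limits it to the intervention group, and the abstract gives 15 sessions. For controls, the study design section says "Those in the control group will not receive any rehabilitation programs during the study".

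**The concern.** The SSQ asks people how well they hear in daily life. Trained participants will have been told of their progress over 15 sessions and asked what training has done for their daily conversations. Controls have no training sessions in which either could happen. The prompting comes after allocation and in one arm only, so randomisation does not balance it.

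A higher SSQ score in the trained arm could therefore mean better everyday hearing, or readier reporting of a benefit that participants have been invited to look for. The comparison cannot tell these apart. The SSQ is the outcome that the protocol ties to its ultimate purpose, so a favourable SSQ result is likely to be cited as evidence that training helps in daily life.

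**Working it through.** **Step 1. What differs between arms before the follow-up SSQ**

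| Feature | Intervention | Control |
|---|---|---|
| Training sessions | 15 | none |
| Progress feedback | every session | none possible |
| Question on daily impact of training | yes, described with the session feedback | not applicable |
| SSQ at baseline | completed by the researcher | completed by the researcher |
| SSQ at both follow-ups | mode not stated | mode not stated |

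The text on feedback refers to all participants, but it is set in training sessions, which only one arm has. The asymmetry therefore follows from what the article states. It does not depend on who holds the pen at follow-up.

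**Step 2. Inputs for an illustration of size**

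The documents give no figure for reporting bias, so there is none of theirs to reproduce on this point. From the Sample size and Data analysis sections I take 14 per group after dropout, 18 per group recruited (14/(1 − 0.2) = 17.5, rounded up to 18) and a significance level of 0.05. Whether 14 follows from the means and SDs in that section is a separate question and does not affect this one.

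Assumptions: there is no true effect, reporting in the trained arm is shifted by b SD with b between 0.3 and 0.5, and the test is a two-sided two-sample t-test at one visit. The protocol plans a repeated-measures ANOVA, so the t-test is a simplification.

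**Step 3. Calculation**

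The noncentrality is b × √(n/2) on 2n − 2 degrees of freedom. The rejection probability is the noncentral t probability outside ± the critical value.

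- n = 18 per arm: √(18/2) = 3, df = 34, critical value 2.03.
  - b = 0.3: noncentrality 0.90, rejection 14.1%.
  - b = 0.5: noncentrality 1.50, rejection 30.8%.
- n = 14 per arm: √(14/2) = 2.65, df = 26, critical value 2.06.
  - b = 0.3: noncentrality 0.79, rejection 11.9%.
  - b = 0.5: noncentrality 1.32, rejection 24.7%.

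For a wider range of b: a shift of 0.2 SD gives 9% at 18 per arm and 8% at 14, and a shift of 0.8 SD gives 65% and 53%. With no shift the rate is the nominal 5%.

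These rates describe the total reporting shift, whatever its source. The part due to the daily-impact question alone cannot be worked out from the documents.

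**The case against.** **The baseline sentence cannot create a difference.** The statement that the researcher fills in the SSQ concerns the visit before training. The Study status section says enrolment is done and allocation is still to come, so this step probably precedes allocation too. A measure taken in the same way in everyone at that stage does not separate the arms. This stands, and the point does not rest on that sentence.

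**Researcher completion at follow-up is an inference.** A reader might conclude that the follow-up SSQ is also researcher-completed, because those visits are called interviews. The protocol uses the same word for a baseline visit that includes otoscopy and audiometry, so it may mean no more than a visit. The documents leave the mode open.

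**One person in both roles, at every session, is also an inference.** A reader might infer that the same researcher records the SSQ and asks trained participants about benefit at each session. The two sections do not say it is the same person, and session feedback is given by an examiner. The sentence on daily impact carries no frequency of its own; the words about every session belong to the sentence before it.

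**Masking of assessors may be described elsewhere.** The article is a condensed account, so its silence on this is no finding. Masked assessors would in any case neither blind participants nor undo the prompting that the article prescribes.

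**The main cause remains.** Participants know whether they had 15 sessions or nothing, and self-completed forms do not change that. This is correct. The proposal removes only the part of the bias that the study procedures add.

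**The SSQ is not primary.** The primary outcome is a speech recognition score, and the other two secondary outcomes are tests. This is a reason for moderate priority but not for leaving the SSQ as it is.

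**Conclusion.** The point holds in a limited form. The protocol prescribes benefit-related contact in one arm only and then compares the arms on a self-report scale covering the same domain. This can add an SSQ difference that is not a hearing benefit.

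The size is unknown. Under an assumed shift of 0.3 to 0.5 SD, the false-positive rate on a single SSQ comparison would be roughly 12% to 31%, depending on the shift and on whether 14 or 18 per arm are analysed, against a nominal 5%. These figures are illustrative only.

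The documents do not support a claim that the trial's main conclusion is compromised, because the primary outcome is performance-based and is not the subject of this point. The change should be made, as a matter of moderate priority.

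**What to change.** 1. Take the question on daily impact out of the training period, or ask it only after the five-week SSQ. Session feedback and the training itself stay as they are.
2. State that the focus group takes place after the five-week assessment.
3. Have participants complete the SSQ themselves at all three visits, before any testing or discussion of progress, and state this mode in both assessment sections. The inclusion criteria require a diploma or higher degree, so self-completion is realistic.
4. If baseline SSQs have already been taken by interview, retake them in the new mode before allocation. If that is not possible, keep the interview mode throughout and use an interviewer from existing staff who does not deliver the training. A change of mode between baseline and follow-up would bring a problem of its own.
5. State as a limit on the SSQ conclusion that participants know their arm.

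The cost is printed forms, protocol wording and, where needed, a repeat of the baseline questionnaire; no added staff. The downsides are some skipped items, which a completeness check that does not discuss the answers can limit, and the loss of one retention prompt.

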### Data analysis

Central tendency and dispersion indices (mean and standard deviation) will be used in descriptive analysis of data. In data analysis and for determining the reliability of the Persian version of the coordinate response measure (CRM) corpus, paired t-test and Pearson correlation will be used in the case of normality of data; otherwise, Spearman test will be employed, and one-way ANOVA will be utilized for determining intra-class correlation coefficient.

In part 2 of the research, repeated measures ANOVA values will be used for inter-group comparisons and two-way ANOVA will be employed for comparison among groups. SPSS software (V20.0, IBM Corporation, New York, USA) will be used for statistical data analysis and the significance level for all tests will be 0.05.

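### Baseline reading span is measured because working memory is said to influence the primary outcome, yet the Part 2 analysis names no covariate and so gives up possible precision

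*Protocol article*

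**What the plan says.** In the assessments before training, the protocol introduces working memory and says why it is measured: "Since the working memory have more influences on the informational masking tasks". The measure is the Persian Reading Span test, and the same item labels it an outcome: "and then recall the final word of each sentence (secondary outcome". The primary outcome comes from the masking test itself: "Measure informational masking score using the test constructed in Part 1 (primary outcome".

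In the assessments after training, reading span "also will be evaluated immediately after training and 5 weeks after that", and its role is restated: "This score and the scores of ‘synthetic sentence identification test’ and ‘Persian reading span test’ will be the secondary outcomes of the interventions".

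For Part 2 the Data analysis section says that "repeated measures ANOVA values will be used for inter-group comparisons and two-way ANOVA will be employed for comparison among groups". It names no covariate and does not say which of the two analyses, or which term within them, decides the primary outcome.

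The design section describes simple 1:1 randomisation and adds: "The two groups will be matched for age and gender". Working memory is not among the matching variables. The Sample size section sets 18 people per group, from 14 plus an allowance for 20% dropout.

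**The concern.** A variable that is measured before treatment and believed to influence the primary outcome is a natural baseline covariate. The protocol holds that belief and collects the value, but the analysis it names has no place for it. That role does not match the reason given for the measurement.

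Two things are at stake in a trial of 36 people. First, variance that the protocol itself thinks is partly explainable may stay in the error term. Second, if the arms differ by chance on working memory, an unadjusted analysis does not correct for it. How far either matters depends on which test decides and on how strongly working memory relates to what that test compares.

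**Working it through.** **Inputs from the protocol.** 18 per group, 14 before the dropout allowance; two-sided alpha 0.05; SDs of change 25.17 (intervention) and 18.15 (control); planned difference 37.5 − 25.17 = 12.33. The root-mean-square SD is √((25.17² + 18.15²)/2) = √(962.95/2) = 21.94.

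**Input not in the protocol.** The correlation r between baseline reading span and the outcome, given group and the baseline masking score. It is assumed, with a range of 0 to 0.5.

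**The plan's own sample size.** The dropout step reproduces: 14/0.8 = 17.5, so 18. The 14 does not. With the difference squared in the denominator, n = (1.96 + 0.84)² × 962.95/12.33² = 49.7, so 50 per group. At 18 per group, power for 12.33 is about 39% (37% by the noncentral t). This is a separate and larger problem, given here only as context.

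**Chance imbalance.** The standardised difference between arms in mean baseline reading span has standard error √(2/n).
- n = 18: 0.333; P(difference above 0.5 SD in either direction) = 0.134.
- n = 14: 0.378; the same probability is 0.186.

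These assume equal arms and no indirect balancing through age and gender.

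**What an imbalance would do.** An imbalance of 0.5 SD shifts an unadjusted change comparison by 0.5 × r × 21.94, where r is now the correlation with change. That is 3.3 points at r = 0.3 and 5.5 points at r = 0.5, against the planned 12.33. At r = 0 the shift is zero.

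**Precision.** Take as reference an ANCOVA with group and baseline masking score (N − 3 residual degrees of freedom) and add reading span (N − 4). The average ratio of effective variances is

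(1 − r²) × (1 + 1/(N − 5)) × (t with N − 4 df / t with N − 3 df)².

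At N = 36 the last two factors are 1.0323 × 1.0024 = 1.035. At N = 28 they are 1.0435 × 1.0042 = 1.048.

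| Assumed r | Variance ratio, N = 36 | Meaning at N = 36 | Variance ratio, N = 28 |
|---|---|---|---|
| 0 | 1.035 | about 3.5% loss | 1.048 |
| 0.2 | 0.993 | under 1% gain | 1.006 |
| 0.3 | 0.942 | worth about 6% more participants | 0.954 |
| 0.4 | 0.869 | worth about 15% more | 0.880 |
| 0.5 | 0.776 | worth about 29% more | 0.786 |

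Setting the ratio to 1 gives break-even at r = √(1 − 1/1.0347) = 0.18 for N = 36 and √(1 − 1/1.0479) = 0.21 for N = 28.

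**The loss is an average, not a ceiling.** If reading span is unrelated to the outcome but the arms differ on it by 0.5 SD, variance at N = 36 rises by the factor 1 + 0.25 × 18/(4 × 17) = 1.066. With the t factor this is 1.069, a loss of about 7%.

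**The case against.** **An article may leave covariates to a fuller plan.** This is a fair point, and giving a reason to measure something does not commit the trial to adjusting for it. But the article does name the Part 2 models and does assign reading span a role. The point is therefore about a better use of stated elements, not about a missing detail, and it is a suggestion, not an error.

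**The repeated measures already protect the comparison.** This largely stands. A group-by-time test on scores before and after training removes any stable effect of working memory on score level. Only its relation to change remains, and the stated reason concerns the tasks, not change. The protocol does describe working memory as needed for learning, and the intervention is a learning programme, so a relation to change is plausible; its size is unknown. A comparison of post-training levels, such as a two-way ANOVA of post scores, would have no such protection.

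**A reader might infer that the unadjusted analysis is biased, or that imbalance is frequent.** The documents support neither. Randomisation keeps the unadjusted comparison valid on average, and a difference above 0.5 SD in 13% to 19% of trials is not the usual case. The cognitive screen, the education requirement and the age limits may also narrow the spread of working memory, which could lower the correlation.

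**Adjustment may cost more than it gives.** This is true below r of about 0.18, or 0.21 with 28 completers. The possible loss is small, but the gain is not assured.

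**Conclusion.** The point holds as a modest improvement. The protocol calls working memory influential on the primary outcome's tasks, measures it at baseline, and then names analyses that do not use it. The result is a possible loss of precision and no correction for chance imbalance, not an invalid test. It applies in full only if post-training levels are compared. If group by time decides, it is limited to the relation between working memory and change, and the Data analysis section does not settle which applies.

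The size rests on an unstated correlation: from an average loss of about 3.5% at r = 0 to a gain worth about 29% more participants at r = 0.5, with 36 analysed.

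It would be wrong to expect adjustment to rescue the sample size. With r taken as the correlation with change, power at 18 per group moves from about 39% to about 42% at 0.3 and 50% at 0.5, and reaches only 66% at 0.7.

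**What to change.** In the Data analysis section, name as the Part 2 primary analysis an ANCOVA, or an equivalent mixed model, of the post-training informational masking score on group, baseline informational masking score and pre-training reading span. Fix this before allocation, which the Study status section describes as still to come. Use only the pre-training reading span as a covariate, because training could alter later values; those stay secondary outcomes. Naming this analysis also settles which comparison decides.

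The cost is a sentence or two and no new data. Reading span takes one degree of freedom. If it proves unrelated to the outcome, the average variance loss is about 3.5% at N = 36 or 4.8% at 28 completers, and somewhat more if the arms happen to be imbalanced on it (about 7% for a 0.5 SD difference at N = 36). The sample size needs its own correction.
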